### Randomisation

Allocation in this study was by cluster randomisation. The unit of randomisation was the school. Individual randomisation was inappropriate for this study as the teaching had to be done in the open classroom, even if lessons were individualised for each student. Consequently it was essential all students in a particular school were allocated to receive the same treatment (either the intervention or usual care).

Randomisation occurred after schools were stratified by type (Special Education Schools/Special Education Units/High Support Needs Schools) and location (Major City/Inner Regional/Outer Regional). Location was categorised according to the Accessibility/Remoteness Index of Australia classification
[23]. Within each stratum, schools were ranked according to the expected number of participating adolescents. Using the ranked list within each stratum, schools were formed into pairs. A list of computer-generated random numbers was used to allocate either the intervention or usual care treatment to the first of each pair; the second in each pair was allocated the alternative treatment.

### Intervention

The intervention school adolescents received the Health Intervention Package, consisting of: an *Ask Health Diary*, an *Ask Project Curriculum Strategy Booklet* and a CHAP health check for use by the adolescent, their parents/carers and GPs. The usual care group received their usual education and medical care. The *Ask Health Diary* component involved the adolescent and the teacher in the classroom, and the adolescent, parent/carer and GP in the surgery. In schools the *Ask Health Diary* was used as a curriculum resource for teaching.

The *Ask Health Diary* has four principal sections: personal details about the adolescent; advocacy tips; guidance for the GP; and health records. By using the first section called “All About Me”, the student learned how to fill in practical details, such as names and addresses of all the health professionals involved in the person’s health care. The student could also role-play attending a GP consultation.

From the second section, “Health Advocacy Tips”, the teacher could use lessons to teach the adolescent tips for general good health. For example, they could be taught practical knowledge about the doctor’s surgery, and skills in organisation for before, during and after going to the doctor. Picture pages assist in communicating symptoms, and diary pages permit keeping track of potentially problematic areas such as menstruation, bowel, bladder, epilepsy and other relevant issues.

The third section, “For the Doctor” provided the GP with information about significant, often unrecognised or poorly managed health problems that adolescents with intellectual disability have, such as inadequate immunisation or constipation, as well as practical tips for doctors and clinic staff, and a syndrome co-morbidity check list.

The fourth section “Medical Records” includes a list of commonly missed problems to be checked, and areas for new findings (e.g. hearing and vision impairments) and actions taken or planned. Additional pages allow recording of diagnoses, operations, medications, immunisations and other histories of relevance.

The *Ask Project Curriculum Strategy Booklet* developed in the pilot provided teaching ideas, strategies and resources to assist teachers with their planning.

The CHAP component of the package involved interactions between the adolescent, the parent/carer and the GP. The adolescent and their parent/carer filled out the first part of the CHAP booklet. This collected a broad history of the adolescent’s health and provided the GP with information that may have needed further investigation. The second part of the booklet was for the GP, who was asked to review the history provided, and then to perform a targeted health examination and record findings. The booklet also acted as an educational tool for GPs, as it gave syndrome-specific physical and mental health problems and prompted the GP in relation to unrecognised or poorly managed disease and unmet preventative health needs.

Based on the pilot study teacher interviews, the *Ask Health Diary* was scheduled to be incorporated into the curriculum throughout the first two terms in the intervention group schools. At the end of Term 2 the diaries were to be sent home and the CHAP booklets sent to the parents/carers, who were to be asked to complete the history gathering section of the CHAP and make an appointment to see the GP during Term 3. Teachers were asked to recommend to carers that the *Ask Health Diary* be used for subsequent on-going contact with the GP and other health service providers. Research staff contacted parents/carers in July 2008 to ensure they had received a diary from the school. A diary was immediately forwarded directly to participants who reported they had not previously received one.

### Data collection

Baseline surveys were sent to educators in both the control and usual care groups. Five months after baseline teachers who taught the program were sent an exit survey. For all adolescents, carer baseline and exit surveys were sent and GP data collected. Carer exit surveys, sent 26 months after baseline, were the same for both intervention and usual care groups, with the addition of CHAP and diary-specific items regarding their usability and perceived benefits for the intervention group. After each GP visit, the CHAP health check booklets were returned to the research team by the carers of adolescents in the intervention group. Evidence of health promotion, disease prevention and case-finding activities were extracted from GPs clinical records 28 months after baseline and after all participants would have had an *Ask Health Diary* for at least 14 months. Qualitative interviews of educators and adolescents occurred after completion of the educational component of the intervention.

#### Baseline surveys

Baseline surveys were sent to educators and carers at the commencement of the intervention. Educator surveys aimed to gather data on age, sex, position and experience of the educator; communication methods of students; school record keeping of students’ current medical information, previous teaching of health related matters and the educator’s concept of advocacy. Carer surveys asked about the age and sex of the adolescent; the aetiology of their intellectual disability; their abilities; and for an assessment of their health. Information on household demographics, their medical record keeping, communication with the school and their reasons for and difficulties involved in their participation in the project were also requested. A measure of the adolescent’s health advocacy skills and the Short Form of the Developmental Behaviour Checklist (DBC-P24)
[24] was also included. Schools were contacted to provide participant’s IQ and Adaptive Behaviour scores.

The pilot study
[25] found that some parents have low literacy skills and for this reason responding to a questionnaire might be problematic; so telephone interviews were offered when both the baseline and exit surveys were distributed and again on follow-up. All carers who had not responded received two telephone reminder calls.

#### Qualitative interviews

Semi-structured interviews were conducted with a small convenience sample drawn from three groups of individuals from the intervention group: adolescents, their parents/carers and teachers. Teachers were invited to interview in July 2007, which was as soon as practicable after teaching the program. Questions were designed to elicit information around the following themes: how and how often the diary was used in the classroom; difficulty or ease of use in the classroom; and suggestions for improvement for use as a teaching tool. Feedback about the perceived benefits of the diary was also requested.

Adolescents and their carers recommended by these schools were interviewed separately in June 2008 after they had completed the CHAP review. The adolescents were interviewed face-to-face at school. Conducting interviews with young adults who have an intellectual disability was a challenge. The researcher who conducted these interviews was an experienced special education teacher and researcher, who had worked extensively with adolescents with intellectual disability. The semi-structured interviews took place at each school in a quiet location where the students were comfortable. The interview schedule was designed to find out how students used the diary and how it was helpful to them. Care was taken to develop rapport with each student and visual prompts, such as displaying a copy of the *Ask Health Diary* to remind the students what the questions were about, were used.

For the parents/carers, questions were designed to elicit information around the following themes: styles of communication; barriers and opportunities for communication; methods of working with GPs; styles of advocacy and determination of decision-making processes during doctor visits, particularly with regard to the CHAP. Interviews with parents/carers were conducted by telephone. We asked for feedback on how the intervention package assisted, or otherwise, participants’ interactions with their GPs; on how advocacy skills were improved; on the tool used in the health review; and on how the intervention package might be improved or altered.

#### Exit surveys

The results of the face-to-face teacher interviews conducted after teaching the program were used to inform the teachers’ post-intervention survey which was distributed at the end of Term 3. All teachers reported to have taught the program were asked about their teaching method, the use of the diary, any problems they faced, and for suggestions to improve the diary. Items were designed to allow them to rate their effectiveness in teaching this material, report any perceived gains for adolescents and their possible future use of the diary. They were also asked to indicate the effect of the program on their expectations of students.

All parents/carers received a post-intervention postal survey at least 12 months after receiving the *Ask Health Diary* and over 16 months after the median CHAP health check date. They were asked about the use of the diary and the CHAP. Items from the baseline on household demographics, the DBC-P24, the measure of health advocacy and the assessment of the adolescent’s health were repeated in this exit survey. Items on residential mobility and their lifestyle and living situation were also included.

#### Health outcome data

In September 2009 we began the process of collecting data from the participants’ usual GPs. A letter was sent to each practice manager advising them of our wish to come and collect the data. We requested copies of all medical records, including correspondence and results of investigations from January 2006 to date of contact with the practice. Approximately one week later this was followed up with a phone call to the practice manager and a date set for data collection. For security reasons, the data were collected from practices by project staff rather than being posted or faxed. Most practice records were computerised and practice managers or doctors produced a print-out of all the data which we collected. In non-computerised practices, photocopies of files were obtained if possible.

Data on medical disorders recorded, past and family histories, allergies, smoking and alcohol consumption, immunisations, current medications, health screening, traumatic injuries, hospitalisations, weight management and the use of the diary was extracted from the notes provided by the GPs. The diagnosed medical disorder was then coded according to both the International Statistical Classification of Diseases and Related Health Conditions (ICD-10) and the International Classification of Primary Care (ICPC-2-R) systems. If there was no diagnosis made, the presenting symptoms were coded. New diagnoses were then identified. A medical professional with extensive experience in the field of intellectual disability checked all ICD codes and new diagnoses. Challenging behaviour is a major issue in this population and much data was available in the GP records collected. All reported challenging behaviours as defined by Emerson
[26] were recorded. The data extraction process was refined from study methods successfully used in other projects conducted by the research team
[6,7]. Although we attempted to mask data extractors to a participant’s treatment status, in practice this was not wholly successful as in many cases the GP had recorded in the notes that his patient had attended his surgery for a CHAP. In a previous research project where the same data extraction tool was used, no difference was found when comparable patterns of health actions were recorded for individuals who received the CHAP regardless of whether or not the extractor was masked
[6].

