### Sample size

We estimated there would be 2,403 adolescents aged 13 to 18 years and registered at SES or SEU, based on Education Department data from the year prior to study commencement. Approximately 80% of these adolescents would have intellectual disability; meaning approximately 1900 students would be eligible for the study. We estimated that around 60% of schools would choose to participate in the study, and that within each school 95% of eligible individuals would participate. Consequently we expected to have a total sample size of around 1,000 adolescents (80% x 60% x 95% of 2403). We estimated participants would be grouped into around 50 clusters (assuming that an average of 20 (SD = 7.5) adolescents with intellectual disability would attend any one school). Thus we expected that each of the intervention and usual care groups would comprise 500 students from 25 schools.

One of the primary outcomes of interest is detection of vision or hearing impairment, which previous studies have shown has a current rate of around 10% in this population
[12,13]. With an assumed intra-class correlation coefficient (ICC) of 0.03, the design effect for this analysis is 1.57, without consideration of matching. On this basis, the study would have 90% power to detect an increase in the detection of vision impairment to 19% due to the intervention, at the 5% level of significance. For a condition with a current impairment rate of 20%, the study will have 90% power to detect an improvement to around 30% through the intervention. The matched-pairs design will have greater power, depending on the within-pair correlations, so the above estimates are conservative. The assumption of a maximum 0.03 for the ICC is plausible, based on a reported ICC (0.01) in an adult population
[7]. For analyses of major subgroups, e.g. examining increases within adolescents with Down syndrome, an estimated 25% of the sample distributed across clusters, the study would have 80% power to detect increases of 10% to 24%, or 20% to 37%.

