#### Quantitative

Percentages of detection of health screenings and health promotion activities initiated, and responses to postal questionnaires will be compared between the intervention and the usual care group using data extracted from medical records. The individual will be the unit of analysis. For continuous outcome variables, a mixed-effects linear regression model will be used to compare the outcomes between comparison groups, with allowance made for cluster and matching effects. For categorical outcomes, a mixed-effects logistic regression model will be used. Sub-group analysis of adolescents at particular risk, such as those with Down syndrome will also be performed.

The primary analyses will be based on the ‘intention-to-treat’ (ITT) principle; all individuals with evaluable data for the outcome under investigation will be analyzed in the group they were randomized to, regardless of treatment received. Additionally, ‘per protocol’ (PP) analyses will be conducted where there have been large deviations from the planned intervention; all individuals with evaluable data for the outcome under investigation will be analyzed according to the treatment received. Any such analyses will be clearly labeled as such and cautiously interpreted as perhaps indicating the maximum theoretical potential of these programs. The PP analyses will consist of three comparison groups according to the timing of the treatment received. The three groups are ‘intervention early’, ‘intervention late’, and ‘no intervention’. The ‘intervention early’ group will consist of individuals whose teachers reported they received their *Ask Health Diary* at the time they were scheduled to, or within 3 months of the time they were scheduled to, and parents/carers confirmed this had been received. The ‘intervention late’ group will consist of individuals who teachers reported they received their *Ask Health Diary* at least three months later than they were scheduled to and those who, when their parents/carers were contacted in July 2008, reported they had not received a diary. The ‘usual care’ group will consist of individuals randomized not to receive an intervention. The separate effects of the CHAP health check, the *Ask Health Diary* and the *Ask Project Curriculum Strategy Booklet* will be explored by comparing outcomes for individuals according to the number, and timing, of components of the health intervention package they received.

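### Extractors were in many cases unmasked by CHAP entries, and the reassurance cited covers only health actions in CHAP recipients, so differential extraction between arms and biased coding of judgement items are not excluded

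*Protocol article*

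**What the plan says.** All of the following is in the protocol article.

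- **Masking (Health outcome data).** Masking of the data extractors was attempted, but "in practice this was not wholly successful as in many cases the GP had recorded in the notes that his patient had attended his surgery"; the visit in question was the CHAP.
- **Reassurance (same section).** The article points to earlier work with a shared instrument ("In a previous research project where the same data extraction tool was used") and reports that masked and unmasked extraction agreed there: "no difference was found when comparable patterns of health actions were recorded for individuals who received the CHAP regardless of whether or not the extractor".
- **Items needing judgement (same section).** Disorders were coded to two classifications. For visits without a diagnosis: "If there was no diagnosis made, the presenting symptoms were coded". A further step separated new from existing conditions: "New diagnoses were then identified". Reported challenging behaviours were recorded as well, and so was use of the diary.
- **Second check (same section).** "A medical professional with extensive experience in the field of intellectual disability checked all ICD codes and new diagnoses". Whether this person was masked is not stated.
- **Role of these data.** Under Sample size: "One of the primary outcomes of interest is detection of vision or hearing impairment". Under Quantitative, detection of health screenings and health promotion activities "will be compared between the intervention and the usual care group using data extracted from medical records".
- **Files obtained (Results, Health outcome data).** 195 usual care, 161 intervention with the CHAP and 80 intervention without it, 436 in all.

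**The concern.** Detection bias in a record review is a difference between arms: files of one arm are searched more thoroughly, or their ambiguous entries are read more generously. Comparing masked with unmasked extraction among CHAP recipients shows whether knowledge of the CHAP changed what was taken from CHAP files. It does not show how completely files without a CHAP entry were searched. Nor, as described, does it reach the items where a reader has most discretion: whether a diagnosis is new, how to code a symptom when no diagnosis was made, and whether an entry is challenging behaviour.

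The main between-arm comparison of detection rests on these records. The article also plans to compare outcomes by the number and timing of components received. There the CHAP entry nearly coincides with the exposure being compared, so any such bias would act undiluted.

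**Working it through.** **1. The planned effect used as the yardstick.** Inputs from Sample size: 500 per arm, mean cluster size 20, ICC 0.03, 10% against 19%, 5% level.

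- Design effect = 1 + (20 − 1) × 0.03 = 1.57, as stated.
- Effective number per arm = 500 / 1.57 = 318.5.
- Two-sided power for 10% against 19% = 0.899, against the stated 90%. The figure reproduces.
- Planned difference = 19 − 10 = 9 percentage points.

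**2. What the reassurance covers.**

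| | Health actions | New diagnoses, symptoms without a diagnosis, challenging behaviour |
|---|---|---|
| CHAP recipients | covered by the earlier project | not mentioned |
| Files without a CHAP | not mentioned | not mentioned |

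One cell of four is covered.

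**3. How far CHAP entries can unmask.** The article gives no count behind its admission, so only a ceiling can be worked out.

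- Intervention files = 161 + 80 = 241. At most 161/241 = 67% of them are exposed.
- Of all files, at most 161/436 = 37% are exposed.
- If every CHAP was noted, and no usual-care file mentions one, a file without an entry is usual care in 195/(195 + 80) = 195/275 = 71% of cases. Absence of the entry is informative, but not decisive.

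Diary mentions could mark further intervention files. The article gives no number for these.

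**4. Illustrative size.** Let the true rate be *p* in both arms. Let a share *a* of events be captured in CHAP files and a share *b* in files without a CHAP entry.

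- Observed intervention rate = *p*(161*a* + 80*b*)/241.
- Observed usual-care rate = *pb*.
- Spurious difference = *p*(*a* − *b*) × 161/241.

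The earlier check bears on whether *a* depends on masking. It gives no information on *b*. Take *p* = 10% (Sample size) and assume *a* − *b* = 5% to 15%; this range is not in the document.

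- Low: 10 × 0.05 × 0.668 = 0.33 points.
- High: 10 × 0.15 × 0.668 = 1.00 point.

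For CHAP completers against usual care, the factor 161/241 drops out and the range is 0.5 to 1.5 points.

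**The case against.** The strongest reply has five parts.

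- **The check is relevant.** A CHAP entry acts directly only on CHAP files, where an expectant reader might over-extract. The earlier project examined that kind of file with the same tool. This stands: the check is useful evidence on one side of the comparison. It leaves the other side untested.
- **The 80 intervention files without a CHAP.** A reader might infer that under-extraction would fall on usual care alone, which would put the intention-to-treat inflation at 0.5 to 1.5 points. The documents do not support that. These 80 files also lack a CHAP entry, so they would share the loss, and the range falls to 0.3 to 1.0.
- **Usual-care files and the marker.** It is tempting to state that no usual-care file mentions a CHAP. The article says only that this group had its usual care, so this is an inference.
- **The checker.** A reader might infer that the medical professional was unmasked. The article does not say so, and silence in a condensed article is not evidence. The check of codes and new diagnoses is a partial safeguard. It cannot restore events never extracted, and the article does not say that it covered challenging behaviour.
- **Outcomes and source.** The screening and health promotion comparisons are largely health actions, the category the earlier check covered, and the judgement items are not named as primary outcomes. Detection of vision or hearing impairment may still involve some judgement. The earlier report is not at hand and may hold a wider comparison than the sentence conveys.

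The article also discloses the unmasking openly and does not claim that the earlier project settles the matter. The fault lies in how little the reassurance covers.

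**Conclusion.** The point holds with limits. On the text shown, the reassurance applies to health actions in CHAP recipients and does not exclude differential extraction between arms or biased coding of judgement items. A reader might go further and infer that the results are biased towards the intervention. The document does not show this: no bias is demonstrated, and its direction and size are unknown.

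The ceiling for exposure through CHAP entries is 67% of intervention files and 37% of all files. The illustrative inflation of about 0.3 to 1.0 points is at most about one ninth of the planned 9. It rests on an assumed loss of 5% to 15% in files without a CHAP entry, a 10% true rate in both arms, every CHAP being noted in the file, and no CHAP entries in usual-care files. This is modest for the main comparison and larger for comparisons by component received. It is worth acting on because the remedy is cheap and the quantitative analysis is still described in the future tense.

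**What to change.** 1. Before the arms are compared, have the same medical professional confirm codes, new diagnoses and challenging behaviour from a listing with arm, school and any mention of the CHAP, the diary or the study removed. If this was already done masked, say so.
2. Add a sensitivity analysis of the main comparison that counts only events backed by a dated test result, immunisation entry, referral reply or prescription.
3. Restrict the reassurance to health actions in CHAP recipients, and state that differential search of files without a CHAP entry remains untested.

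The cost is some data-management time to prepare the listing, assuming the extracted text was kept in usable form, and one extra analysis. No further assessor is needed. Steps 1 and 2 reduce the role of judgement but cannot recover events that were never extracted, which is why step 3 is needed as well.
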